## Abstract

**Background:**

Osteoporosis-related fractures are a significant public health concern. Interventions that increase detection and treatment of osteoporosis, as well as prevention of fractures and falls, are substantially underutilized. This paper outlines the protocol for a pragmatic randomised trial of a multifaceted community-based care program aimed at optimizing the evidence-based management of falls and fractures in patients at risk.

**Design:**

6-month randomised controlled study.

**Methods:**

This population-based study was completed in the Algoma District of Ontario, Canada a geographically vast area with Sault Ste Marie (population 78 000) as its main city. Eligible patients were allocated to an immediate intervention protocol (IP) group, or a delayed intervention protocol (DP) group. The DP group received usual care for 6 months and then was crossed over to receive the interventions. Components of the intervention were directed at the physicians and their patients and included patient-specific recommendations for osteoporosis therapy as outlined by the clinical practice guidelines developed by Osteoporosis Canada, and falls risk assessment and treatment. Two primary outcomes were measured including implementation of appropriate osteoporosis and falls risk management. Secondary outcomes included quality of life and the number of falls, fractures, and hospital admissions over a twelve-month period. The patient is the unit of allocation and analysis. Analyses will be performed on an intention to treat basis.

**Discussion:**

This paper outlines the protocol for a pragmatic randomised trial of a multi-faceted, community-based intervention to optimize the implementation of evidence based management for patients at risk for falls and osteoporosis.

**Trial Registration:**

This trial has been registered with clinicaltrials.gov (ID: NCT00465387)

## Background

Osteoporosis, a chronic condition characterized by decreased bone mass and increased risk of fractures, is a significant public health concern. It affects over 200 million people worldwide[1], an estimated 10 million people in the US[2], 4 million people in the UK[3] and 1.4 million people in Canada[2,4]. Fragility fractures are the clinical consequence of osteoporosis. While vertebral fractures can cause back pain, loss of height and disability, hip fractures have a more significant impact on quality of life leading to loss of function, and admission to long-term care. [5-9] It is estimated that 1 in 5 people who suffer a hip fracture will die during the first year and less than one third gain their pre-fracture level of function. [2] Moreover, the economic impact of this condition is considerable, with the total acute care cost of osteoporosis estimated to be over $1.3 billion per year in Canada[9], $20 billion in the US[10] and over €30 billion in Europe. [11,12] Given that the proportion of people aged 65 and older is increasing, this will likely lead to an even more significant burden of disease. [4,12]

Osteoporosis increases the risk of fractures in elderly patients who fall. [4] Falls are the leading cause of accidental death among people aged 65 years of age and older, and also account for significant morbidity, including fracture, impaired mobility, decreased quality of life due to fear of falling, depression, admission to long-term care facilities, and death. [13-18] Estimates vary, but approximately 20% of falls among the elderly result in serious injury requiring medical attention, and 2% to 10% of these falls result in fractures. [13,14,18-21] Because of the morbidity and mortality associated with falls, they result in marked costs for the health care system and are a major health concern. [22]

For the prevention of fractures, a substantial body of evidence supports detection and treatment of osteoporosis in high-risk patients, including appropriate bone mineral density testing and therapy with calcium, vitamin D, and drugs that decrease bone resorption or increase bone formation. [23] For example, bisphosphonates reduce the risk of future osteoporosis-related fracture by 40 to 60%, with fracture reduction apparent within a year of starting treatment. [23] Similarly, research suggests that interventions targeting both intrinsic and environmental risk factors reduce the risk of falls in older people. [24]

Despite the incorporation of this evidence from randomized trials into clinical practice guidelines, these interventions are considerably underutilized. [25-29] According to a recent systematic review, the proportion of individuals with a fragility fracture who received a diagnostic test for osteoporosis or a diagnosis from a physician ranged from 1.7% to 50%. [27] And, it is unclear how many patients who experience a fracture are assessed for risk of falls.

These care gaps highlight the finding that additional effort is needed to ensure that appropriate knowledge translation is achieved to optimize management of patients at risk for falls and fracture. This study was designed to help fill this knowledge to practice gap. The primary objective of this study was to determine if a multicomponent, complex, community-based, integrated care strategy could optimize the evidence-based and guideline-concordant management of people at high risk for falls and fractures. This study was developed by a community partnership because of a locally identified need to address these evidence to practice gaps. Given the significant disease burden of falls and fractures in the local community, the partnership decided to implement and evaluate a multi-faceted intervention to enhance care.

## Methods

Between March 2003 and January 2006, we conducted a randomized trial of a multifaceted community based intervention to optimize care of patients at risk for falls and fractures. Two parallel trials were conducted in this group of patients. We did not conduct a factorial trial because we had no reason to believe that osteoporosis treatment and falls assessment would not be managed independently. Previous studies have shown this to be true. [30,31] An economics evaluation was carried out in parallel to this randomized controlled trial to evaluate the costs and consequences as well as cost-effectiveness of applying the intervention.

### Setting and Study Population

This study was completed in the Algoma District of Ontario, Canada, a geographically vast area with Sault Ste Marie (population 78 000) as its main city. The study represented a partnership among consumers, providers and other stakeholders interested in reducing falls and fractures in the community. It was conducted by the Group Health Centre (GHC), a multidisciplinary, multi-specialty, not-for-profit health service community centre, in partnership with Sault Area Hospital (SAH), a facility with 250 active beds. When the study was initiated, the Group Health Centre had 44 000 registered patients. Distinguishing features of the GHC are multiple types of health care professionals integrated within a health care delivery system, capitation funding and an electronic medical record system (EMR). The study was also completed in partnership with the Algoma Community Care Access Centre; the Algoma Health Unit; and the Slips, Trips and Falls Committee of Sault Ste Marie Safe Communities Partnership, a community-based falls prevention coalition.

Patients were eligible for inclusion in the study if they were community-dwelling, aged 55 years or older, able to give informed consent, and were identified to be at risk for a future fracture according to one of the following criteria:

1. attended the hospital Fracture Clinic for a non-pathological fracture of the vertebrae, hip or wrist or BMD in the past year with a T-score of ≤ -2.0;

2. attended the hospital Emergency Department with a fall and found to be at high risk for falls as defined by a Timed Up and Go[32] result of greater than 14 seconds; or,

3. were self-referred or referred by a health care provider because of perceived high risk of fracture, and identified as a high risk for falls defined by a Timed Up and Go result of greater than 14 seconds.

Patients were excluded if they were already receiving appropriate therapy for osteoporosis as outlined in the Osteoporosis Canada guidelines. [23]

### Interventions

#### Osteoporosis Risk Assessment and Management

This intervention was multifaceted and consisted of providing evidence-based management strategies for osteoporosis to both the patients and their primary care providers. Following randomization, a bone mineral density (BMD) test was facilitated for participants if it had not been done within the past year, and the results were sent to the primary care physician along with relevant prescribing information based on the Osteoporosis Canada guidelines. [13] A complete list of the patient's medications was compiled from two sources and provided to physicians: (1) the patient's pharmacy records; and (2) home visits conducted by the study nurses. Medications associated with increased risk of fracture were identified, and physicians were asked to assess this list of flagged medications (Appendix).

Patients received personalized counseling from the research nurse about osteoporosis, including a written summary of the proposed management plan. They also received educational materials on calcium and vitamin D, risk factors for osteoporosis, and their BMD results. For those few individuals without a primary care physician, the same materials were provided but patients were encouraged to visit a walk-in clinic or the emergency department.

### Falls assessment and management

The intervention was multifaceted and consisted of providing patient-specific evidence-based recommendations targeted to reduce falls risk to both the patients and their primary care providers. A research nurse assessed participants in their home and completed the Berg Balance Scale[33], the InterRAI Screener[34,35], a medication review and an assessment for orthostatic hypotension. The InterRai screener is used to assess the elderly individual to identify those who merit further assessment in order to prevent or stabilise early functional or health decline. Medications associated with increased risk of falls were identified through review of pharmacy records and home visits and primary care providers were asked to assess this list of flagged medications (Appendix).

The criteria for appropriate referral for physiotherapy and occupational therapy services were based on the results of the InterRAI Screener and the Berg Balance Score. Physiotherapy interventions were tailored to each patient and included strengthening exercises, gait and balance training, and referral to activities such as T'ai Chi classes. Occupational therapy interventions were also tailored to each patient and included home environmental assessment and cognitive testing. Details on the interventions provided by the rehabilitation therapists will be described in additional detail in the results paper for this study. All therapists completed standard reporting forms indicating their recommended interventions and barriers to patient compliance with these recommendations.

Patients received personalized counseling from the research nurse about fall prevention including a written summary of the suggested management plan. They also received educational materials including a checklist for falls prevention.

### Allocation and Blinding

Eligible patients were randomized using a computer generated randomization scheme under supervision of the study biostatistician, into an immediate intervention protocol (IP) group or to a delayed intervention protocol (DP) group. All members of the DP group received usual health care during the first 6 months of the main study and then were able to receive the intervention after this period. Patients, physicians and outcomes assessors could not be blinded to the fact that patients were part of a falls and fracture prevention study. All patients were followed-up at 6 and 12 months after the completion of the initial assessment.

### Outcomes and Data Collection

The primary outcome for the osteoporosis study was appropriate osteoporosis management based on the 2002 clinical practice guidelines for osteoporosis in Canada. [23] This was the most current evidence-based guideline available for use at the time of study onset and was generally consistent with US and UK guidelines. The primary outcome for the falls study was the implementation of appropriate falls risk assessment at 6 months. Measurements of outcomes were obtained through patient records (obtained through the Electronic Medical Record), therapists' reports, and pharmacy data. A standardized chart review of the Electronic Medical Record was the primary source of data for both groups.

Secondary outcomes included the number of falls and fractures as recorded in monthly patient diaries. Follow-up telephone calls every 3 months were used to obtain this data and completed patient diaries were mailed to the investigators at study end. Quality of life was measured using the OPTQoL[36], a disease-specific quality of life questionnaire. After the main study was completed at 6-months, and the DP group crossed-over to receive the intervention, all patients were followed up for a further 6 months.

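### For the falls primary outcome, therapists' reports may supplement the chart review, but the only ones described are intervention forms with no stated delayed-group counterpart before month 6

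*Protocol article*

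**What the plan says.** All references are to the protocol article.

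- **Sources.** Outcomes and Data Collection names three: "Measurements of outcomes were obtained through patient records (obtained through the Electronic Medical Record), therapists' reports, and pharmacy data". It then ranks them: "A standardized chart review of the Electronic Medical Record was the primary source of data for both groups".
- **Therapists' reports.** The only ones described are under Falls assessment and management, as part of the intervention: "All therapists completed standard reporting forms indicating their recommended interventions and barriers to patient compliance with these recommendations".
- **Comparator.** Allocation and Blinding gives DP usual care for the first 6 months, which is the window of the falls primary outcome.
- **Whose record.** Setting and Study Population presents the electronic medical record as a feature of the GHC, which had 44 000 registered patients; the main city has 78 000 people. Entry is through the hospital fracture clinic, the emergency department, or self- or provider referral. GHC registration is not a criterion. The Economics substudy names the hospital's medical record separately, and only for costs.
- **Blinding.** Allocation and Blinding states: "Patients, physicians and outcomes assessors could not be blinded to the fact that patients were part of a falls and fracture prevention study". It does not say whether outcome assessors knew the arm.

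**The concern.** Primary source does not mean only source. The article states no rule that stops a therapist's form from supplying an event that the chart lacks. The falls outcome is the implementation of appropriate falls risk assessment, so paperwork produced by the intervention can itself document that outcome. A DP patient assessed in usual care leaves a trace only if the chart holds it, or if some therapist's report exists that the article does not describe.

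The gap is widest for patients outside the GHC record. There the chart review finds little or nothing in either arm, but an IP patient may still have a study form.

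Scoring adds a second route. Whether management was appropriate can require judgement. The stated reason for not blinding assessors is that they knew a falls and fracture study was under way. That does not prevent hiding the arm when the outcome is scored.

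Both routes would tend to favour the intervention. The planned two-sample test of proportions cannot reveal such a bias, and a larger sample would not remove it.

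**Working it through.** **1. Which sources are tied to one arm**

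| Source listed for outcomes | Tied to one arm before month 6? | Bears mainly on |
|---|---|---|
| GHC chart review | No; stated for both groups | both outcomes |
| Pharmacy data | No restriction stated | osteoporosis medication |
| Therapists' reports | Described only as intervention forms | falls assessment |

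Only the third row is asymmetric as written, and it concerns the falls outcome.

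**2. Inputs for an illustration**

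The plan gives no detection rates, so there is no figure of its own to reproduce on this point. From Sample size and Analysis come 200 patients, 10% loss and a 40% rate for each outcome (arm not stated). With 1:1 allocation, which is assumed because the ratio is not stated, 200 × 0.9 / 2 = 90 analysed per arm. The true rate is set to 40% in both arms, so there is no real effect.

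The following are assumptions:
- The share q of patients outside the GHC record is 20-44%. The upper end is (78 000 − 44 000)/78 000 = 34/78 = 0.436. It is crude: it takes all registrants to live in the city and ignores age and the wider district.
- Half of the events in DP patients outside the record are missed.
- No record shows an event that did not happen.

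**3. Full detection in IP**

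Observed DP rate = 0.4(1 − q) + 0.4 × q × 0.5 = 0.4(1 − 0.5q). The relative shortfall is 0.5q, that is 10-22%. The rejection rate is exact for the two-sided pooled z test at 90 per arm.

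| q | DP observed | False difference | Rejection at nominal 5% |
|---|---|---|---|
| 0.20 | 0.360 | 4.0 points | 8.9% |
| 0.30 | 0.340 | 6.0 points | 13.7% |
| 0.44 | 0.312 | 8.8 points | 23.8% |

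**4. Study forms fill only part of the gap in IP**

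Let IP patients outside the record miss a quarter of events: observed IP rate = 0.4(1 − 0.25q).
- q = 0.20: 0.380 against 0.360, a 2.0-point difference, rejection about 6%.
- q = 0.44: 0.356 against 0.312, a 4.4-point difference, rejection about 10%.

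**5. Equal detection in both arms**

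With both arms at 0.360, or both at 0.312, rejection is about 5%. Incomplete records alone do not inflate the type I error. They do cost power: at 90 per arm and true rates of 40% against 60%, the normal approximation gives 77% with full detection and 68% with 90% detection in both arms.

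**The case against.** The strongest reply is that one standardized chart review is the declared primary source in both groups, and that the rest is silence in a condensed article. Much of this stands, and it rules out several stronger readings:

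- **That outcome sources differ by arm in general.** Only the supplementary therapists' reports fit that description. Nurse home visits and the compiled medication list are described as parts of the intervention and are not listed as outcome sources.
- **That both primary outcomes are equally affected.** The sample size section frames the osteoporosis outcome as receipt of appropriate medications. Pharmacy data are not confined to one arm, and the therapists' forms are described as recording recommendations and barriers to compliance, not prescribing.
- **That GHC registration biases the comparison by itself.** It precedes randomisation and should balance between arms. It matters only if study forms fill the gap in IP alone.
- **That assessors were unblinded to arm.** The sentence concerns knowledge of the study. Knowledge of the arm is an inference, and a full protocol may describe masking.
- **That 9-24% is an estimate of the error rate.** It needs IP to miss nothing and DP patients outside the record to lose half their events; the documents support neither figure.

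It is also fair that nothing says DP patients seen by therapists in usual care lacked reports, and that discarding every study record would drop genuine IP assessments.

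What remains is that the article lists a source it describes only inside the intervention, draws charts from one provider's record while recruiting more widely, and gives a reason for not blinding that does not reach masking to arm.

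**Conclusion.** The point holds in limited form. For the falls outcome, following the article as written can find IP events that would be missed in DP, chiefly among patients outside the GHC record. The osteoporosis outcome is less exposed. Masking to arm at scoring is neither described nor ruled out by the reason given.

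The direction, in favour of the intervention, is plausible; the size cannot be determined from the documents. Under the assumptions set out above, the false difference runs from nothing with equal detection to about 9 points in the least favourable case, with rejection between about 5% and 24%. This supports a cheap improvement, not a change without which the trial could not be interpreted.

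**What to change.** 1. Score both primary outcomes by one fixed, written algorithm, applied to an extract in which allocation and study letters are masked and entries after month 6 are removed.
2. Rest the primary falls analysis on the chart review common to both arms. Report the result with and without events documented only on study therapists' forms.
3. Add a sensitivity analysis restricted to patients registered with the GHC at randomisation.

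**Cost.** No new data sources are needed, but there is some extra abstraction. The study ran from March 2003 to January 2006, so this may mean going back to charts already reviewed. Masking will be incomplete where the chart itself reveals the intervention. Genuine IP actions recorded only on study forms will not count in the primary falls analysis, which can bias that analysis against the intervention; this is why both versions should be shown. The registrant-only analysis will be less precise.

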### Economics substudy

The costs that will be included are: nursing time, administrative time (e.g. booking appointments), home visit travel, costs of health care professional continuing education, costs of community education, and the costs of program materials. Interviews with program staff and cost information from the GHC administration will be used to calculate program costs. Research project evaluation costs will be excluded from program costs. Costs to the health care system as well as costs to the patient will be collected from the GHC electronic medical record, the Sault Area Hospital medical record, or via patient interview. The intervention program costs and health resource utilization were collected at 6 months post-enrollment, 1 year post-enrollment and 2 years post-enrollment. Analyses will be done from the perspectives of the public payer and the patient. Effectiveness and cost information will be applied to a decision analytic model that has been specifically designed to determine the cost effectiveness of various treatments for osteoporosis. To assess the long term cost-effectiveness of the program for both men and women of various ages, separate long term projection models for both men and women by age would be required. The only model that is currently available is a model based on post-menopausal osteoporosis. [37,38] Therefore, it is in this patient population that the long term cost-effectiveness will be estimated based on the intermediate outcomes from this study.

### Qualitative substudy

A sample of program staff, patients and physicians will be interviewed about their experiences in the study and to explore issues around costs, adherence to the intervention and whether the material on osteoporosis and falls prevention was discussed by patients and physicians. Individual, semi-structured interviews will be facilitated by an experienced interviewer. Purposive sampling will be used to identify patients who did and did not receive appropriate therapy. Their primary care physicians will also be invited to participate in individual interviews. Domains of enquiry will focus on knowledge of osteoporosis and falls prevention information and perceptions of use of this evidence in decision making and clinical care. Barriers and facilitators to implementation will also be explored. Interviews will be audiotaped and the tapes will be transcribed. Any unique participant identifiers will be removed from the transcripts. Two investigators will independently analysis the transcripts using content analysis to identify themes. NVivo will be used to analyse the data. Investigators will use the constant comparative method to challenge the development of their themes and will use memos to track the development of their themes and analytical strategy.

